1. Does the prevention program Looking for Meaning lead to a significant reduction of depressive symptoms and a significant enhancement of wellbeing, satisfaction with life, and quality of life in elderly people with depressive symptoms, in comparison with a no-treatment control group?

2. Which prognostic factors (demographic, clinical symptoms, mastery), in combination with the intervention, predict lower or higher effects on depressive symptoms, wellbeing, satisfaction with life and quality of life?

3. What is the incremental cost-utility in the treatment group as compared to the control group?

4. Which are the working components of the intervention, leading to reduction of depression and enhancement of wellbeing, mastery and satisfaction with life, according to the participants?

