##### Economic evaluation

The aim of the economic evaluation is to estimate the incremental cost-utility in terms of quality-adjusted life years (Qualy) gained in the treatment group, as compared to the non-treatment group. The economic evaluation is based on the EQ-5d and the Tic-P. Costs of the intervention itself are estimated as well. Measures are described below.

9. An increase of quality of life as measured with the EQ-5D.

The EuroQoL EQ-5D is a pre-scored health classification system that is defined over five domains of health: mobility, self-care, usual activity, pain/discomfort and depression/anxiety [27-29]. Each of the five domains is categorized into three severity levels; 0 (none), 1 (some) and 2 (severe). Responses are combined by a scoring algorithm to produce a summary utility score between -0.594 and 1.0, where 1 represents the state of best imaginable health. Values correspond with Quality-adjusted life years (Qualy) gained or lost. We use an index based on the Dutch population, in accordance with the Dutch TTO tariff [29]. In our study, we also use the EQ-5D as a clinical outcome measure indicating one's perceived quality of life.

10. A decrease in costs of receiving (in)formal health care as measured with the TIC-P.

Cost data are collected using the TIC-P [30]. Costs are defined from a societal perspective and include direct and indirect costs related to receiving formal and informal health care. Production losses in both paid and unpaid work are also covered by the TIC-P. These costs arise when people are absent from work, or work less efficiently due to depression, for example. Production losses will be estimated with the help of the TIC-P.

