### Analyses

The analyses will be performed according to the íntention to treat' principle. Therefore, all missing values were imputed. In order to replace the missing values by plausible estimates, we will use the regression imputation procedure as implemented in Stata version 9.1 [31].

We will calculate effect sizes for the immediate improvement of the experimental and the control group on the primary and secondary outcomes by dividing the absolute difference between the post-treatment average score and the pretreatment average score by the pretreatment standard deviation. To establish the maintenance of improvement of both groups, effects sizes will be calculated by dividing the absolute difference between the follow-up average score and the post-treatment average score by the pretreatment standard deviation. For between-group effect sizes, the effect size of the experimental group will be subtracted from the effect size of the control group. Effect sizes of 0.56–1.2 can be assumed to be large, while effect sizes of 0.33–0.55 are moderate, and effect sizes of 0–0.32 are small [32].

In the cost-effectiveness analyses, we will calculate the pre-post changes in costs and identify which respondents show a moderate to large improvement in depressive symptoms in both conditions. These respondents changed reliably, and could thus be considered a 'success'. Then we calculated the incremental cost-effectiveness ratio (ICER) across the experimental and control condition, which represents the incremental costs (or savings) per 'success' (i.e. moderate to large improvement in depressive symptoms) in the experimental condition relative to the control condition. Uncertainty will be assessed by means of non-parametric bootstrapping (2,500 times) of the data of the individual respondents.

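### The stated economic question is incremental cost per QALY, but the only economic analysis described is cost per depression 'success', which the EQ-5D does not enter

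*Protocol article*

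**What the plan says.** The Background section, research question 3, asks: "What is the incremental cost-utility in the treatment group as compared to the control group". Under Methods/Design, Economic evaluation, the aim is repeated with its unit: "The aim of the economic evaluation is to estimate the incremental cost-utility in terms of quality-adjusted life years (Qualy) gained in the treatment group". The same section names the sources: "The economic evaluation is based on the EQ-5d and the Tic-P". It fixes the tariff ("We use an index based on the Dutch population, in accordance with the Dutch TTO tariff"), takes a societal perspective and says that the costs of the intervention are estimated too. On the link from utility to QALY it says only: "Values correspond with Quality-adjusted life years (Qualy) gained or lost". Table 1 schedules both instruments at t0, t1 and t2.

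The Analyses section then gives the economic analysis: "we will calculate the pre-post changes in costs and identify which respondents show a moderate to large improvement in depressive symptoms in both conditions". Respondents who improve that much count as successes, and an ICER is formed, "which represents the incremental costs (or savings) per 'success' (i.e. moderate to large improvement in depressive symptoms". Uncertainty comes from 2,500 bootstrap resamples. No QALY calculation and no cost per QALY appear there.

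**The concern.** The question and the analysis use different effect measures. A cost-utility ratio has QALYs in its denominator; the described ratio has depression responders. An analyst who follows the Analyses section exactly would deliver a result for a question that the article does not pose, and none for the one it does.

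The economic part is not incidental. Cost-effectiveness is half of the declared purpose in the Design section, and the Discussion presents the economic evaluation as the first for life review. If both ratios are eventually calculated but only one is described in advance, the choice of which to emphasise could be made after the data are seen.

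A second issue concerns the cost side. The phrase for the cost change does not say which two time points it spans, so the cost numerator may cover only part of follow-up.

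**Working it through.** The article states no ICER, QALY or cost figure, so there is nothing to reproduce. The check sets the sections side by side.

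| Element | Research question 3 and Economic evaluation | Analyses |
|---|---|---|
| Type of ratio | Cost-utility | Cost-effectiveness |
| Effect | QALYs gained | Number of 'successes' on depressive symptoms |
| Effect instrument | EQ-5D, Dutch tariff | Depressive symptoms (the CES-D is the trial's measure) |
| Cost | Societal, TIC-P, plus intervention costs | Change in costs, time points not defined |
| Uncertainty | Not stated | 2,500 bootstraps |

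**Step 1: the two ratios.**
- Asked for: (difference in mean cost) / (difference in mean QALYs).
- Described: (difference in mean cost change) / (difference in proportion with success).

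To turn the second into the first, one needs the QALY difference per additional success. The article gives no such mapping, so the conversion cannot be made.

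**Step 2: does the EQ-5D enter anywhere else?** It is also declared a clinical outcome, so the standardised effect sizes in the Analyses section may apply to it. Those are mean changes divided by the pretreatment standard deviation. They give neither a QALY total nor a cost per QALY.

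**Step 3: the cost window.** The Overview under Data collection puts t1 at 3 months after t0 and t2 at 6 months after t1, so follow-up is 3 + 6 = 9 months, or 0.75 year. The Analyses section uses 'post-treatment' for t1 and 'follow-up' for t2. Read consistently, the cost change runs from t0 to t1: 3/9 = 33% of follow-up. The remaining 6/9 = 67% is left out, although TIC-P and EQ-5D are both collected at t2. This is the likely reading, not a certain one.

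**Step 4: what a QALY calculation on the scheduled data looks like.** With utilities u0, u1 and u2 at 0, 0.25 and 0.75 year and linear interpolation:

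QALY = 0.25 × (u0 + u1)/2 + 0.50 × (u1 + u2)/2 = 0.125 u0 + 0.375 u1 + 0.25 u2

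The weights sum to 0.75, the horizon in years. All three inputs are already in Table 1.

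**The case against.** The strongest defence is that an article condenses a fuller plan. The Analyses section does not say that its ratio replaces a cost-utility analysis, and the article already names the utility instrument, tariff, cost instrument and perspective. Area-under-the-curve mechanics and baseline adjustment are details that an article may leave out. That stands to this extent: a fuller plan could contain a QALY analysis, so the claim can only be about the analysis as described. It does not remove the point, because the article is not silent. It fixes an effect measure, a ratio and an uncertainty method, and the effect measure conflicts with the aim.

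One could also restore consistency by rewording question 3 and the aim as cost-effectiveness, the label used in the Design section. That is possible, but it would give up the declared aim although the data for it are collected.

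Four stronger readings are tempting and are not supported:
- **That the plan will use utilities as QALYs without weighting by time.** The sentence linking the two is a loose description of an instrument, not a planned computation. Any size put on such an error depends on an assumed path. A gain that is immediate and held for 0.75 year would be overstated by 1/0.75 − 1 = 33%; one that rises linearly to t2 yields 0.375 of its final value and would be overstated by 1/0.375 − 1 = 167%. The plan does not compute the ratio to which these would apply, so they do not measure an error in it.
- **That a difference in cost change is invalid as such.** Under randomisation it estimates the between-arm cost difference for the post period, net of baseline. The open question is which period is covered.
- **That intervention costs are ignored.** The Economic evaluation section says that they are estimated.
- **That the result could not be compared with any other programme.** It could be set beside depression programmes that report cost per responder.

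**Conclusion.** The mismatch is in the text. The question and aim are incremental cost per QALY from the EQ-5D and TIC-P; the only economic analysis described is incremental cost per depression success, without the EQ-5D. As described, the analysis does not answer research question 3, one of four. The cost change is undefined and probably omits the 6 months from t1 to t2; that rests on reading the section's terms consistently, and the TIC-P recall window, which would help to settle it, is not given.

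The effect is confined to the economic evaluation. The primary analysis of depressive symptoms is untouched, and no bias in a number can be quantified because no economic figure is stated.

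**What to change.** In the Analyses section, add an incremental cost per QALY analysis:
- QALYs per respondent as the area under the EQ-5D utility curve over t0, t1 and t2 (0.75 year), with the between-arm difference adjusted for t0 utility;
- societal costs, including intervention costs, over the same t0 to t2 period, with a statement of how the TIC-P reports cover that period;
- the planned 2,500 bootstraps applied to cost-QALY pairs.

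Keep cost per success as an additional result, and define the time points of its cost change. In the Economic evaluation section, say that utilities become QALYs only when weighted by time.

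No new instrument, visit or participant is needed, since both questionnaires are already scheduled at all three times. The cost is a change of wording and a little analyst time.

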### Quantitative study

#### Data collection

##### Overview

Table 1 provides an overview of the economic and effect measurements. As a part of the intake and selection interview, we administer the Center for Epidemiological Studies Depression Scale (CES-D), in order to screen the participants. The outcome is considered the CES-D baseline score for those included; the course starts shortly thereafter. Data at t0 (baseline), t1 (effect; 3 months after t0), and t2 (retention; 6 months after t1) are collected by means of a questionnaire. Demographics and additional personal characteristics are recorded at t0 only, and evaluation questions about the participant's experience with the intervention are asked only at t1. Except for that, the three questionnaires are identical.

**Table 1 T1:** Measurement overview per time (intake, t0, t1, and t2) and research section (clinical, economic and qualitative study)

Variables per research section	Instrument	Intake	T0	T1	T2
Screening and selection					
Examine for depression if CES-D ≥ 16	MINI	×			
Clinical effect evaluation					

*Primary outcome*					
Depressive symptoms	CES-D	×		×	×
					
*Secondary outcomes*					
Anxiety	HADS-D		×	×	×
Locus of control; mastery	Pearlin Mastery Scale (5 items)		×	×	×
Satisfaction with life	MANSA (12 items)		×	×	×
					
*Reminiscence functions*	RFS (4/8 subscales)				
Boredom reduction			×	×	×
Bitterness revival			×	×	×
Identity			×	×	×
Problem solving			×	×	×
					
Economic evaluation					

Cost associated with the receipt of care	TIC-P		×	×	×
Quality of life	EQ 5-D		×	×	×
					
Qualitative study					

Interviews with participants			×			
Observation			×			

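### The cost-effectiveness 'success' is described as reliable change, but the only cut-off the article gives (0.33 SD, set for group means) cannot support that for an individual

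*Protocol article*

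**What the plan says.** The point lies in the Analyses section of the protocol article, in two consecutive paragraphs.

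The first paragraph defines effect sizes for each arm by "dividing the absolute difference between the post-treatment average score and the pretreatment average score by the pretreatment standard deviation". It then gives the interpretive bands: "Effect sizes of 0.56–1.2 can be assumed to be large", while "effect sizes of 0.33–0.55 are moderate, and effect sizes of 0–0.32 are small". These bands are introduced for differences between average scores.

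The second paragraph turns to cost-effectiveness. The analysts will "identify which respondents show a moderate to large improvement in depressive symptoms in both conditions". Of these people it says: "These respondents changed reliably, and could thus be considered a" success. The ICER is the incremental cost, or saving, for each such success in the course arm relative to the video arm.

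The article states no respondent-level cut-off, no reliable-change index and no reliability figure for the CES-D. The Primary outcome section says only that the scale's psychometric properties are good in older populations.

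**The concern.** The same words, moderate and large, are used first for group means and then for single respondents. The mean of some 80 to 100 people has little measurement error, so a shift of 0.33 SD in it can be meaningful. One person's change is the difference of two fallible scores, and 0.33 SD may be less than the scale's noise. If so, the statement that these people changed reliably is wrong.

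The interpretation of the ICER is at stake. A reader who takes the article at its word would read cost per success as cost per person whose improvement exceeds measurement error. Under the cut that the text implies, the success count would also include many people whose true level of symptoms had not moved.

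**Working it through.** The article gives no figure on this point to reproduce. The check asks what a cut of 0.33 SD implies for one respondent.

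**Inputs**
- Cut: 0.33 pretreatment SD, the lower edge of the moderate band (Analyses). As an alternative, 0.56 SD, the lower edge of the large band.
- CES-D reliability r: not given. Assumed 0.70 to 0.95.
- Only falls in score count as improvement.

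**Formulas.** In units of the pretreatment SD, each score has error variance 1 − r. For a person with no true change, the difference of two scores has mean 0 and SD √(2(1 − r)). Hence:
- chance of being labelled a success = 1 − Φ(cut / √(2(1 − r)));
- reliable-change limit = 1.96 × √(2(1 − r)), or 1.645 × √(2(1 − r)) for a one-sided 5% rule.

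Example at r = 0.80: √(2 × 0.20) = 0.632; 0.33 / 0.632 = 0.522; 1 − Φ(0.522) = 30.1%; limit 1.96 × 0.632 = 1.24 SD.

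| Assumed r | SD of error change | Unchanged people past 0.33 SD | Unchanged people past 0.56 SD | 1.96 limit (SD) | 1.645 limit (SD) |
|---|---|---|---|---|---|
| 0.70 | 0.775 | 33.5% | 23.5% | 1.52 | 1.27 |
| 0.80 | 0.632 | 30.1% | 18.8% | 1.24 | 1.04 |
| 0.85 | 0.548 | 27.3% | 15.3% | 1.07 | 0.90 |
| 0.90 | 0.447 | 23.0% | 10.5% | 0.88 | 0.74 |
| 0.95 | 0.316 | 14.8% | 3.8% | 0.62 | 0.52 |

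Under the 1.96 limit, 2.5% of unchanged people would be labelled improved, whatever r is.

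**Reliability needed for the claim to hold.** Setting the cut equal to the limit and solving gives r = 1 − (cut / c)² / 2.
- 0.33 SD, c = 1.96: 1 − (0.1684)² / 2 = 0.986.
- 0.33 SD, c = 1.645: 1 − (0.2006)² / 2 = 0.980.
- 0.56 SD, c = 1.96: 1 − (0.2857)² / 2 = 0.959.

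For any r below 1 − 0.33² / 2 = 0.946, a change of 0.33 SD is smaller than one SD of pure error change.

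**Whole-number scores.** With simulated CES-D scores rounded to integers from 0 to 60 and an assumed SD of 6 to 10 points, the cut is about 2 to 3 points. The share of unchanged people labelled successes is then about 21% to 37% for r from 0.90 to 0.70. The normal approximation is not driving the result.

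**Effect on the ICER denominator.** The denominator is the difference in success proportions between arms. As an illustration, assume normal change scores, an intake-to-follow-up correlation of 0.6 (SD of change √(2 × 0.4) = 0.894), and the planning effect of 0.35 SD from the Sample size section. Compare the 0.33 cut with 1.07 SD, the 1.96 limit at r = 0.85.
- No control improvement: at 0.33, 0.509 − 0.356 = 0.153; at 1.07, 0.210 − 0.116 = 0.095 (from unrounded proportions).
- Control improvement of 0.7 SD: at 0.33, 0.790 − 0.660 = 0.129; at 1.07, 0.491 − 0.340 = 0.152 (from unrounded proportions).

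The choice of cut changes the denominator, and the direction depends on how much controls improve.

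**The case against.** Several objections deserve weight.

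**The cut is inferred.** The article never gives 0.33 SD as a threshold for a respondent, and a condensed article may leave that rule to a fuller document. This stands as a caveat. Still, the band is the only meaning of moderate that the article supplies, and the claim of reliable change is made in the article itself. Starting success at the large band would not rescue the claim unless reliability were at least about 0.96 on the 1.96 rule.

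**The percentages rest on assumed reliability.** This is correct, and they should be read only as a range. The required reliability of 0.98 to 0.99 does not depend on that assumption.

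**Chance labelling occurs in both arms.** This is also correct. A reader might infer that the ICER is biased in favour of the course, or that the stated share of all successes is false. Neither follows. The percentages describe people with no true change, and mislabelling them does not by itself create a difference between arms.

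**A stricter rule need not worsen the ICER.** A reader might infer that a reliable-change rule must make the course look less cost-effective. The illustration above shows that it can go either way.

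**Regression to the mean.** The CES-D intake score is used both to select people and as the baseline ("The outcome is considered the CES-D baseline score for those included"), so a reader might infer that regression to the mean adds further apparent successes. The Participants section does not support a net direction. Excluding scores below 5 pushes towards apparent improvement, and excluding people with major depression trims the upper end and pushes the other way.

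**Scope is limited.** The cost-utility question in QALYs and the CES-D analysed as a continuous outcome do not use this dichotomy and are untouched.

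**Conclusion.** The concern holds in a limited form. The statement that respondents with a moderate to large improvement have reliably changed is not supported by the only cut-off in the article. At 0.33 SD it would need a CES-D reliability of about 0.98 (one-sided 5%) to 0.99 (1.96 rule).

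If reliability lies between 0.70 and 0.95, which is an assumption, about 34% to 15% of people with no true change would be called successes, against 2.5% under a 1.96 reliable-change rule. The conclusion rests on reading the group-mean band as the individual cut, which is inferred but has no rival in the text.

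The consequence concerns meaning: cost per success is not cost per reliably changed person. The size and direction of the effect on the ICER cannot be fixed from the documents. The point should be corrected before the cost-effectiveness analysis is run, and it leaves the primary clinical outcome untouched.

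**What to change.** Choose one of two routes and state it in the Analyses section.

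1. Define success as a fall in CES-D of at least 1.96 × SD × √(2(1 − reliability)). Give the threshold in CES-D points and name the source of both the SD and the reliability. The trial's own 20-item intake data could supply both.
2. Keep 0.33 SD, state that it applies to individual respondents, and call it a responder threshold. Delete the claim of reliable change, and report the reliable-change definition as a sensitivity analysis for the ICER.

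Either route changes only analysis and wording and needs no new data. The reliable-change rule has a price: fewer successes in both arms, and a limit that some participants may be unable to reach. With reliability 0.90 to 0.80 and an assumed SD of 6 to 10 points, the required fall runs from 0.88 × 6 = 5.3 to 1.24 × 10 = 12.4 points, while people are eligible from an intake score of 5. The number who cannot reach the limit should be reported by arm.

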### Qualitative study

#### Data collection

To answer research question 4, and gain an insight into the working mechanisms of a life-review approach in general and the course 'Looking for Meaning' in particular, we designed a qualitative study.

The study comprises twenty semi-structured interviews with participants of approximately one hour each, and research observations in three different participant groups during six hours in total. Both the interviews and the observations are centered on participants' experiences with the course, with an emphasis on the life review aspect in relation to the participants' personal experiences and clinical outcome measures. The interview questions are typically open-ended and put in a non-leading way. They leave open *if *life review is helpful or effective at all and gives the participants room to also respond negatively.

The audio-taped interviews are transcribed verbatim. The group observations result in detailed notes about the evaluation process and the interactions between participants. They serve as a point of reference when interpreting the interview data; observations might support or contradict the other qualitative findings.

##### Qualitative data analysis

More than one method may apply to analyze qualitative data, including 'code-and-retrieve' methods (33–35). 'Code and retrieve' means that relevant parts of the material are selected or highlighted (coded), extracted, and clustered in the end. In this process, abductive inference combines new and interesting empirical facts from the data in the first place (bottom-up) with previous theoretical knowledge [34], whereas inductive inference is more restrictive and departs from a theoretical framework (top down) to classify the data.

In this study, we will use a top-down, theory driven approach with an emphasis on newly emerging insight irrespective of whether an observation is made repeatedly or can be easily classified. It is added to the quantitative analysis in order to better understand the outcomes. Relevant information can be recognized in relation to, or in contrast with, the knowledge to date. By reading and re-reading the data materials and making notes with in mind the research questions, the researcher yields descriptive and explanatory research outcomes integrated with his or her theoretical knowledge.

